### Exclusion criteria:

1. Pregnancy
2. Breastfeeding
3. A history of or current acute inflammatory joint disease of different origin e.g. mixed connective tissue disease, seronegative spondylarthropathy, psoriatic arthritis, Reiter’s syndrome, systemic lupus erythematosus or any arthritis with onset prior to age 16 years
4. Acute major trauma

5) Therapy within the *previous 60 days* with:

- any experimental drug
- alkylating agents, e.g. cyclophosphamide, chlorambucil
- antimetabolites
- monoclonal antibodies (including infliximab and etanercept)
- growth factors
- other cytokines

6) Therapy within the *previous 28 days* with:

- parenteral or intraarticular corticoid injections
- oral corticosteroid therapy exceeding a prednisone equivalent of 10 mg daily
- present use of DMARDs other than methotrexate

7) Receipt of any live (attenuated) vaccines within 4 weeks prior to baseline

8) Fever (orally measured > 38 °C), chronic infections or infections requiring anti-

microbial therapy

9) Known positive reaction to hepatitis B surface antigen or Hepatitis C antigen

10) Other active medical conditions such as inflammatory bowel disease, bleeding

diathesis, or severe unstable diabetes mellitus

11) Manifest cardiac failure (stage III or IV according to NYHA classification)

12) Progressive fatal disease/terminal illness

13) A congenital or acquired (known HIV-positive status) immunodeficiency

1. 14) a history of lymphoproliferative disease or treatment with total lymphoid

irradiation.

15) A white cell count less than 3.5 x 109/l

16) Platelet count less than 100 x 109/l

17) Haemoglobin of less than 5.3 mmol/l

18) Body weight of less than 45 kg

19) History of drug or alcohol abuse

20) Any concomitant medical condition which would in the investigator’s opinion compromise the patient’s ability to tolerate, absorb, metabolize or excrete the study medication.

21) Inability to give informed consent

22) Mental condition rendering the patient unable to understand the na­ture, scope

and possible consequences of the study and/or evidence of an uncooperative attitude.

Screenings procedures

Screening will be done within 1-2 weeks before baseline to assess the in- and exclusion criteria and to evaluate if all the safety parameters are met. All patients sign their informed consent form before baseline.

Variables and schedule of observations

The following will be determined in accordance with the "Schedule of observations" *(see page 2-3*).

### Background information

Before enrolment in the study, all patients will undergo a full physi­cal examination, and the relevant medical history will be taken. Further to this demographic data will be collected/measured and documented.

The following data will be documented:

- date of obtaining informed consent
- initials, date of birth, sex, race, weight and height
- alcohol consumption and smoking behaviour
- concomitant illnesses, infections, malignancies and treatment
- rheumatoid arthritis disease status and time since RA diagnosis
- DMARD history including infliximab and etanercept, current medication
- changes in dosage of prednison, NSAIDs and methotrexate
- relevant findings in physical examination

### Primary endpoint

The primary endpoint of the study is the percentage of patients with a moderate to good response to adalimumab treatment at 16 weeks according to the Eular response criteria which is also applied in routine rheumatological practice.

A decrease in the DAS 28 value must be ≥ 1.2 at any given timepoint after initiation of treatment for continuation of reimbursement by the insurance company.

| **DAS 28 score at**  **(week 16)** | **Improvement in DAS 28 at week 16 compared to baseline (week 0)** | | |
| --- | --- | --- | --- |
|  | **>1.2** | **> 0.6 en  1.2** | ** 0.6** |
| ** 3.2** | **Good** |  |  |
| **> 3.2**  **and  5.1** |  | **Moderate** |  |
| **> 5.1** |  |  | **None** |

*Tabel 1: Eular response criteria*

Furthermore the primary endpoint of the study is to search for clinical parameters and/or serological markers that possibly distinguish responders from non-responders to TNF-α blockade by adalimumab.

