Prospective study on the effects of adalimumab treatment in patients with rheumatoid arthritis who are naïve for TNF- blocking therapy and patients who do not respond (anymore) to prior treatment with other anti-TNF- medication.

Protocol version 2.1

04-02--2008

[name]

[name]

[name]

[name], PhD

Division of Clinical Immunology and Rheumatology, F4-218

Department of Medicine,

Academic Medical Center/University of Amsterdam

[name]

[contact] [contact] E-mail:[contact]

| *Schedule of Observations* |  | Screening | T=-2 | T=0 | T=4 | T=16 | T=28 | T=40 | T=52 |
| --- | --- | --- | --- | --- | --- | --- | --- | --- | --- |
| *Visit number* |  | **V0** | **V1** | **V2** | **V3** | V4 | **V5** | **V6** | **V7** |
| TNO/insurance request for approval | *(DAS 28)* | X |  |  |  | X |  |  |  |
| Demographics | *Age*  *Race*  *Height*  *Weight*  *Alcohol*  *Smoking* |  | X |  |  |  |  |  |  |
|
| DMARD & biological history | *DMARDs*  *Prednison*  *Biologicals* |  | X |  |  |  |  |  |  |
| Concommitant. medication |  | X | X | X | X | X | X | X | X |
| In- and exclusioncriteria |  | X | X |  |  |  |  |  |  |
| Informed consent |  |  | X |  |  |  |  |  |  |
| mRNA for storage |  |  |  | X | X | X | X | X | X |
| DNA sample (genetic polymorphisms) |  |  |  | X |  |  |  |  |  |
| X-thorax (< 3 mnd voor baseline) |  |  | X |  |  |  |  |  |  |
| PPD (<6 mnd voor baseline) |  |  | X |  |  |  |  |  |  |
| Virology screening | *Hepatitis B, C, HIV* |  | X |  |  |  |  |  |  |
| Urine -HCG | *pregnancy test* |  | X |  |  |  |  |  |  |
| IgM RF, anti- CCP, ANA, ds-DNA |  |  | X |  |  |  | X |  | X |
| Radiological progression | *Sharp modified by*  *Van der Heijde score* |  |  | X (<3mnd accepted) |  |  |  |  | X |
| (X-hands, feet) |
| Routine laboratory testing | *ESR, CRP, Hb, Ht, Leuco’s, Trombo’s, creatinin, ureum, Na, K, ALAT (SBPT), ASAT (SGOT), LDH, Gt, AF, glucose, bilirubine, alkaline phosphatase, protein and albumin,* |  | X | X | X | X | X | X | X |
| *Urine dipstick: glucose, protein, blood* |

| *Schedule of Observations* |  | Screening | T=-2 | T=0 | T=4 | T=16 | T=28 | T=40 | T=52 |
| --- | --- | --- | --- | --- | --- | --- | --- | --- | --- |
| *Visit number* |  | **V0** | **V1** | **V2** | **V3** | **V4** | **V5** | **V6** | **V7** |

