## Design.

A monocenter prospective, exploratory study with a 1 to 2-week screening period and a 52-week follow-up period in 120 RA patients who receive adalimumab treatment in routine rheumatological practice and are TNF- blockade naïve or have failed to (or no longer) respond to other anti-TNF- treatment. There is no group of patients receiving control treatment, since it is considered unethical to withhold active treatment for 52 weeks in patients with active RA. Previous work has shown the efficacy of adalimumab in randomized trials (8;9).

The goal of the present study is to evaluate the response to adalimumab treatment in the TNF- blockade naïve patients and patients who failed on other prior TNF- blocking treatment. Therefore, responders will be compared with non-responders after all included patients have received anti-TNF- therapy in the form of adalimumab. Furthermore the goal is to understand more of the mechanisms underlying the response to anti-TNF- treatment. Adalimumab treatment will be discontinued in patients who do not fulfill the Eular response criteria for improvement (DAS 28) at week 16, according to routine clinical practice.

Patients who discontinue adalimumab at or after week 16 for lack of respons or other reasons will get a final clinical assessment as part of the close out visit. The reason for discontinuation will be noted in the case record form. These patients will not be followed for measurement of clinical parameters. In patients who respond, treatment will be continued and may be extended after the 52-week follow-up period of this study. Patients will be included starting January 2004.

Patients who drop out of the study before week 16 for any reason will be replaced by new patients, the reason of discontiuation will be noted in the case record form (*see withdrawl and replacement of patients)*

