## Duration of study

All patients participating in this study will receive 40 mg (0,8ml) adalimumab by subcutaneous injection every other week after fulfilling all inclusion criteria at baseline. All patients must have approval for reimbursement for TNF-blockade by their insurance company (DAS 28 >3.2). Patients will be seen during the study for efficacy and safety assessments at weeks 4, 16, 28, 40 and 52 using validated and generally accepted evaluation criteria (see laboratory and clinical variables). All visits will be fixed with reference to the baseline visit. Evaluation of ACR 20 and Eular response (DAS 28) will be performed at 16 weeks after initiation of adalimumab. The final clinical assessments will be performed at 52 weeks. If the patient does not meet the Eular criteria for moderate or good response at 16 weeks, adalimumab treatment is discontinued and no further assessments will be done.

Inclusion criteria:

1) Patients with the diagnosis rheumatoid arthritis according to the American Rheumatism Association (ARA) 1987 criteria and in ACR 1991 functional classes I, II, and III *(see appendix)*

2) The patient is naïve for anti-TNF- therapy or has failed other prior TNF- blockers

3) DAS 28  3.2

4) Age > 18 and  85 years old

5) Use concurrent methotrexate treatment (5 - 30 mg/week; stable since at least 28

days before initiation) during the study. Subjects may be taking nonsteroidal anti-

inflammatory drugs, provided the dose and frequency have been stable for at

least 28 days. Subjects may be receiving prednisone therapy  10 mg/day

provided that the dosage has been stable for at least 2 months prior to entry.

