### Withdrawl and replacement of patients

Patients who drop out of the study before week 16 for any reason will be replaced by new patients, the reason of discontiuation will be noted in the case record form.

These patients will be seen for a final clinical assessment as part of the close out visit.

This visit will include physical examination, final assessment of disease activity (ACR, DAS 28, RADAI, SF 36), follow up of previous adverse events. Blood will be drawn for safety screening of clinical heamatology and chemistry parameters. Furthermore final immuno- serology to screen for auto-antibody formation (ANA, anti-ds DNA). Titers of IgM-RF and anti-CCP will also be drawn at this visit.

Premature discontinuation of study

The investigator has the right to discontinue this study at any time for medical and/or administrative reasons. As far as possible, this should occur after mutual consultation. Furthermore adalimumab treatment will be discontinued if there is no reimbursement by the insurance company.

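### Responders with a DAS 28 fall above 0.6 but below 1.2 are both continued and discontinued after week 16, so the week 28 to 52 population is not defined

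*Protocol*

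**What the plan says.** All references are to the protocol.

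- **Primary endpoint.** The endpoint is the "percentage of patients with a moderate to good response to adalimumab treatment at 16 weeks according to the Eular response criteria". Table 1 places the moderate label in the column for a DAS 28 improvement above 0.6 and up to 1.2, in the row for a week-16 score above 3.2 and up to 5.1. The good label is in the column for an improvement above 1.2.
- **Design.** "In patients who respond, treatment will be continued and may be extended after the 52-week follow-up period of this study". No reimbursement condition is attached.
- **Duration of study.** "If the patient does not meet the Eular criteria for moderate or good response at 16 weeks, adalimumab treatment is discontinued".
- **Primary endpoint, on the insurer.** "A decrease in the DAS 28 value must be ≥ 1.2 at any given timepoint after initiation of treatment for continuation of reimbursement".
- **Premature discontinuation of study** (the paragraph after withdrawal and replacement). "Furthermore adalimumab treatment will be discontinued if there is no reimbursement by the insurance company".
- **Schedule of Observations.** The row "TNO/insurance request for approval" is marked at screening and at week 16 (V4), the visit at which the primary endpoint is scored.
- **Design, on patients who stop at or after week 16.** They have a close-out assessment and the reason for stopping is recorded in the case record form. After that: "These patients will not be followed for measurement of clinical parameters".

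**The concern.** Two thresholds operate at the same visit. The response definition accepts a fall just above 0.6, while reimbursement, on which treatment depends, needs a fall of at least 1.2. A patient between the two is a responder whose treatment continues under the Design section and a patient whose treatment stops under the reimbursement sentences. Nothing in the protocol says which prevails.

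What is at stake is the later data. Clinical follow-up ends at the close-out visit, so the rule applied at week 16 decides who contributes to ACR 20/50/70 at weeks 28, 40 and 52, to the one-year efficacy question, and to the week-52 DEXA scan and radiographs. If the reimbursement rule is applied, the responders removed are those with the smallest improvement, and the one-year results among patients still observed would look better for that reason alone. If the EULAR rule is applied, these patients remain.

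**Working it through.** The protocol states no figure to reproduce here, so the check is first logical and then illustrative.

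**Step 1: classify by both rules.** Labelled moderate cell: 0.6 < fall ≤ 1.2 and 3.2 < week-16 score ≤ 5.1. Reimbursement: fall ≥ 1.2, where fall = baseline score − week-16 score.

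| Baseline | Week 16 | Fall | Table 1 | Fall ≥ 1.2? |
|---|---|---|---|---|
| 5.0 | 4.0 | 1.0 | Moderate | No |
| 4.5 | 3.6 | 0.9 | Moderate | No |
| 6.0 | 4.9 | 1.1 | Moderate | No |
| 5.0 | 3.8 | 1.2 | Moderate | Yes |

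The first three patients are responders, so the Design section continues them, but they miss the reimbursement threshold, so treatment stops. Only a fall of exactly 1.2 meets both rules within this cell. The good cell (fall above 1.2) creates no conflict.

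**Step 2: how much of the cell is affected.** On a 0.1-point grid the week-16 score takes 19 values (3.3 to 5.1) and the fall takes 6 (0.7 to 1.2), giving 19 × 6 = 114 combinations. Those with a fall below 1.2 number 19 × 5 = 95. The conflict thus covers 95 of 114 combinations in the only cell labelled moderate. This counts combinations, not patients.

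**Step 3: illustrative number of patients.** The planned number is 120 (Design). The protocol gives no DAS 28 means or SDs, so these inputs are assumptions: baseline normal with mean 5.0 or 5.5 and SD 1.1, restricted to 3.2 or more; fall normal and independent of baseline, with mean 1.0, 1.5 or 2.0 and SD 1.0 or 1.4; the threshold judged at week 16. The quantity simulated is P(0.6 < fall < 1.2 and 3.2 < week-16 score ≤ 5.1).

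- Highest case (baseline 5.0, fall 1.0, SD 1.0): the fall band alone has probability Φ(0.2) − Φ(−0.4) = 0.579 − 0.345 = 0.235. With the score limits the simulation gives 0.151, and 120 × 0.151 ≈ 18 patients.
- Lowest case (baseline 5.5, fall 2.0, SD 1.4): the band alone has Φ(−0.571) − Φ(−1) = 0.284 − 0.159 = 0.125. With the score limits the simulation gives 0.073, and 120 × 0.073 ≈ 9 patients.

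The range is about 7-15% of patients, or 9-18 of 120.

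**Step 4: sensitivity.**
- If a week-16 score of 3.2 or below with the same fall also counts as moderate (that cell is blank in the table as available), the range is about 8-19%, or 10-23 of 120. With every fall above 1.2 also counted as a response, that is 10-31% of responders.
- A second set of assumptions (baseline mean 5.2-5.6, SD 1.1-1.2; fall mean 1.3-2.0, SD 1.2-1.3; correlation 0.3) gives 7.6-12.2% in the labelled cell, about 9-15 of 120. With the blank cell included it gives 9.3-15.0%.
- If one earlier fall of at least 1.2, for example at week 4, satisfies the insurer, the group shrinks but still includes everyone whose fall never reached 1.2. If every visit must qualify, the group grows.

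**The case against.** The strongest reply is that the insurer's threshold is an outside constraint which the protocol merely reports. Adalimumab is prescribed in routine practice, and entry already requires reimbursement approval. The stop in Duration of study runs in one direction: it removes non-responders and does not order that every moderate responder continue. The reimbursement stop can be read as a further ground, and the Design section already provides for stops after week 16 for reasons other than lack of response. This stands in part. Duration of study and the reimbursement stop are compatible with each other. The direct clash is between the unconditional continuation of responders in the Design section and the two reimbursement sentences taken together. That clash remains, because no sentence makes continuation subject to payment.

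The study is also exploratory and uncontrolled, and denominators and cross-tabulations normally belong in an analysis plan. Their absence from the protocol is no defect. Who continues treatment, and is therefore observed, is a protocol matter.

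Two stronger readings are tempting, and the protocol supports neither:

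- **That the week-16 result, or the week-16 comparison of responders with non-responders, changes.** It does not. Response is fixed by EULAR class at that visit, whatever happens to treatment afterwards.
- **That the reimbursement rule removes poor responders before week 16, who are then replaced.** The timing phrase in the reimbursement sentence might suggest this, but the Schedule of Observations marks no insurance request between screening and week 16.

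**Conclusion.** The contradiction is real and follows from the protocol's own thresholds. It does not depend on the signs lost from Table 1, since the labelled moderate cell alone produces it. For responders with a fall above 0.6 but below 1.2, the protocol cannot be followed as written.

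The consequence is confined to what comes after week 16. The population observed from week 28 to week 52 is undetermined, and applying the reimbursement rule would lose the weaker responders selectively.

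The size cannot be derived from the protocol. Roughly 7-15% of patients (about 9-18 of 120) is an illustration for the labelled moderate cell, resting on assumed normal DAS 28 distributions and on judging the threshold at week 16. The existence of the conflict rests on neither assumption.

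**What to change.** - Reconcile Design, Primary endpoint and the premature discontinuation paragraph, and align Duration of study with them, so that one stated rule governs continuation after week 16. Which rule that should be is not for this review.
- State what the timing phrase in the reimbursement sentence means: one qualifying visit, every visit, or the week-16 visit.
- Whichever rule stands, keep responders stopped for reimbursement in the week 28, 40 and 52 denominators, counted as discontinued.
- Report week-16 EULAR class cross-tabulated with a DAS 28 fall of at least 1.2 (yes or no), so that the size of the overlap is visible.

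No new case record form item is needed, because the reason for stopping is already recorded. The cost is a few sentences of protocol wording, one denominator convention and one table.

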### Secondary endpoints

The secundary endpoint of the study is the proportion of patients with a 20%, 50%, and 70% clinical improvement according to the ACR response criteria (11) at 4, 16, 28, 40 and 52 weeks after the initiation of adalimumab treatment. The parameters of disease activity e.g. tender joint count, swollen joint count, patient’s assessment of pain, patient’s global assessment, investigators global assessment, duration of morning stiffness, health assessment questionnaire, DAS 28, SF-36 (short form health survey) and RADAI (12) will be assessed at each time point starting from baseline. Also an assessment of the influence of adalimumab treatment on physical and mental wellbeing in relation to employment status, job-satisfaction and sickleave will be implemented in the form of questionnaires.

In addition we will look at the influence of adalimumab on bonemineraldensity, bonemetabolism.

This will be done by analysing serum and urine markers for bone formation and resorption, performing a DEXA scan before- and one year after adalimumab initiation.

We will look for genetic markers, e.g. genetic polymorphisms in TNF- genes, that may predict diagnosis, efficacy and side-effects of treatment in the individual patient.

In the future micro-array analysis may be done to screen for new markers that distinguish responders from non-responders. Also, immunological responses raised against adalimumab antibodies will be researched, comprising antibody formation and T cell responses.

## **Safety Variables**

### Adverse events

Adverse events observed by the investigator or reported by the patient will be documented as described below in this study protocol. Infections, malignancies and hospitalisation during adalimumab will be noted on a separate page in the case record form.

## **Laboratory variables**

The following laboratory variables will be assessed prior to baseline.

HEMATOLOGY: hemoglobin, haematocrit, red blood cell count, white blood cell count (and if abnormal, differential count), platelet count.

chemistry: glucose, creatinine, sodium, potassium, calcium, phosphate, uric acid, bilirubin (total), alkaline phosphatase, ASAT(SGOT), ALAT(SGPT), LDH, GT, CPK, total protein and albumin, CRP.

urinalysis: semiquantitative (dipstick) for glucose, protein, blood. If protein is positive urine sediment should be done and urinary protein loss (over 24 hours) should be determined quantitatively. Pregnancy test in women with child-bearing potential (β-HCG).

IMMUNOLOGY: ANA, IgM RF, anti ds-DNA, and anti-CCP

at week 0 and week 28 and 52 (also performed at close out visit)

VIROLOGY: HbsAg, HCV and HIV-test at pre-screening

## **Additional variables**

Chest-X ray (<3 months old is acceptable)

PPD skin test (repeat if prior PPD is 6> months ago)

If the PPD skin test is positive, but there are no signs of an active TB on the chest X-ray and the patient does not have any symptoms of an active TB, the patient is allowed to enter the study, but must be treated for possible latent TB prior to the first dose of adalimumab in the trial.

If the PPD skin test is positive and signs of an active TB are visible on the chest X-ray or the patient has symptoms of an active TB, the patient is not allowed to enter the study.

In this study per patient a total volume of approximately 215 ml of blood will be drawn for study purposes over a period of 52 weeks.

## **Clinical variables**

As clinical safety monitoring the following examinations will be performed:

A complete medical history will be taken before enrollment. Interest will be focused on current concomitant diseases and DMARD-history.

Physical examination will be performed at screening. Vital signs (blood pressure, pulse frequency, body weight, oral body temperature) will be determined at each visit.

Any evaluations that are abnormal and considered to be related to the study medication will be followed until they return to baseline or are judged not to be clinically significant.

